## Treatments Potentially Interfering with Vaccine-Induced Immunity

**The following criteria should be checked at each scheduled clinic visit. If any become applicable during the study, the subject will not be required to discontinue, but a separate analysis may be carried out excluding these individuals. See Section 12.2 for definitions of study cohorts and datasets to be evaluated.**

**Any routine immunization deferred as a result of participation in this study, will be administered expeditiously starting 30 days after last receipt of study vaccine.**

- Use of any investigational drug or vaccine other than the study vaccine during the study period
- Administration of chronic (defined as more than 14 days) immunosuppressants or other immune-modifying drugs within six months of vaccination. (For corticosteroids, this will mean prednisone, or equivalent,  0.5 mg/kg/day. Inhaled and topical steroids are allowed.)
- Administration of a vaccine not foreseen by the study protocol during the period starting from 30 days prior to first dose to 30 day after the third dose visit
- Administration of immunoglobulins or any blood products up to 30 days after the last dose of vaccine

## Contraindications to Vaccination

The occurrence, in any eligible study subject, of any event enumerated in Section 6.9.6 (“Dose Discontinuation in Individual Subjects”) represents a contraindication to further immunization of that subject; however, the parent/guardian of such a subject will be encouraged to continue participation in the safety and immunogenicity evaluation for the duration of the study.

## Indications for Deferral of Vaccination

The following adverse events constitute grounds for deferral of vaccine administration at a given point in time; if any one of these adverse events occurs at the time scheduled for vaccination, the subject may be vaccinated later, within the allowable time interval specified in the protocol (see Section 7.1.2), or may be permanently discontinued from further vaccination at the discretion of the investigator (the only withdrawals from follow-up, i.e., from the study proper, would be for withdrawal of consent). The subject must be followed until resolution of the event as with any adverse event (see Section 10.4). If the subject is discontinued from further vaccination, the parent/guardian will be encouraged to keep the subject in the study for the safety and immunogenicity evaluation for the duration of the study.

- Axillary temperature  37.5 °C or evidence of clinical malaria (see Section 7.3.2) at the time of vaccination will warrant deferral of immunization until fever and symptoms resolve.
- Any other condition that in the opinion of the investigator poses a threat to the individual if immunized or that may complicate interpretation of the safety of the vaccine following immunization.

Such subjects will be followed in the clinic until the symptoms resolve or the window for immunization expires. No further vaccination will be performed if the subject does not recover (axillary temperature < 37.5°C or lack of symptoms, as appropriate) within nine days of the originally scheduled vaccination date. The subject, however, will continue to be followed for safety and immunogenicity. **If the subject meets any of the above criteria for deferral on the day of first immunization the PI may elect to exclude the subject from further participation in the study.**

## Safety Plan

### Criteria for Temporary Suspension of Vaccination

If any of the following SAEs occurs, the PI will ensure the temporary suspension of vaccination for all study subjects, and the events will be reported as described in Section 10.5 and in SSP No. MAL036-14.

1) Death in any subject where the cause of death is judged to be related to study vaccine

2) The occurrence in any subject of an anaphylactic reaction to study vaccine

3) The occurrence in any subject of a life-threatening SAE which is judged to be causally related to the vaccine (see definition of “Yes” as regards causality in Section 10.3, pg. 77)

4) The occurrence of a non-life-threatening SAE which is judged to be causally related to the vaccine

5) The occurrence, in one or more subjects, of laboratory abnormalities judged by the PI to be potentially life-threatening and related to receipt of study vaccine

The following findings will mandate temporary suspension of additional doses:

1. In 20 (5%) or more children, occurrence of Grade 3 solicited systemic (not local) AEs judged related to the study vaccine, or
2. In 20 (5%) or more children occurrence of Grade 3 unsolicited AEs judged related to the study vaccine.

NB: a) and b) will come from pooled, blinded data.

### Safety Review Prior to Administration of Consecutive Doses

After each dose, the PI will provide the LMM with a report covering the seven-day post‑dose observation period. This report will detail all SAEs occurring within the seven day period in all vaccinated children, as well as all solicited AEs and all Grade 3 unsolicited AEs for the first 200 children vaccinated. The PI will provide a copy of these reports to the DSMB, MVI, GSK Biologicals, USAID, and SCI. For each event, a statement of causality (event considered related/unrelated to vaccination, according to the PI’s best judgment) will be included. For the first and second doses, the reports will be submitted no less than seven days before the upcoming dose.

Administration of consecutive doses will not proceed until both of the following have occurred:

1. The LMM has reviewed the available safety data (and has had the opportunity to discuss the data with the DSMB, if she feels it necessary), and
2. The PI has determined that none of the SAEs or events outlined in Section 6.9.1 has occurred.

### Procedure for Temporary Suspension of Vaccination

If the PI understands that any of the criteria cited in Section 6.9.1 has been met, he will immediately suspend all further vaccinations and disseminate a brief preliminary report, by electronic mail, within 24 hours, to the LMM, study sponsor, study partners, and the DSMB, notifying them of the suspension.

### Procedures for Resumption of Dosing Following Temporary Suspension of Vaccination

1) Upon determining the need to *temporarily suspend* further vaccinations, the PI will, within three working days, produce a full written report to the DSMB on the incident in question including as much relevant information as possible. Within five working days of receiving the report, the DSMB Chairperson will convene a meeting (via teleconference, videoconference, face-to-face, or a combination of these) with the full membership of the DSMB, plus the LMM, to review and discuss the clinical information, safety data, and general course of events leading to the suspension. During the DSMB’s deliberations, all study partners (the PI, the sponsor [USAMMDA], WRAIR, GSK Biologicals, MVI, SCI, and USAID) will maintain a “standby status” and be available to provide, on short notice, any required information or other input.

2) After due discussion, the DSMB will submit a “verbal” (telephonic or electronic mail) recommendation as to an appropriate course of action to the study sponsor and other “voting” study partners (the PI, WRAIR, GSK Biologicals, and MVI); this will be followed up with a written version of the recommendation within three working days of the meeting. (Copies will be maintained at the study site and with the study sponsor.) Upon receiving the verbal recommendation, the voting partners will decide on the best course of action to be taken. Consultative, or “observer”, study partners (SCI and USAID) will also contribute to this discussion. Unanimous agreement by all five voting partners will be required for resumption of vaccinations.

3) If the DSMB, LMM, and voting partners agree that vaccinations should be recommenced, the HSRRB and the KEMRI ERC will be promptly notified, and the study will go forward with the remaining vaccinations. If, however, the DSMB recommends non-resumption of vaccinations, but the voting partners agree that vaccinations should be recommenced, then the IRBs (PATH/HSPC, the HSRRB, the KEMRI ERC) and US FDA must be consulted and all must concur with this decision before vaccinations resumption.

### Procedures for Permanent Discontinuation of Vaccination

Any decision for a *permanent discontinuation* of further vaccinations will take the form of a formal notification to the study sponsor from the PI. Such notification will come only after due discussion among the voting and consultative study partners and the LMM (as described in Section 6.9.4), and might or might not follow a recommendation for permanent discontinuation from the DSMB. The formal notification will also be provided promptly to PATH/HSPC, the HSRRB, the KEMRI ERC, and the DSMB. Regardless of whether permanent discontinuation of vaccinations occurs for an individual or for the entire study population, safety follow-up (for the entire study duration) and crossover rabies vaccine administration (after study completion) will still be performed.

### Dose Discontinuation in Individual Subjects

Reasons for discontinuation of study vaccine administration in an individual subject include, but are not limited to, the following:

1. Anaphylactic reaction following administration of study vaccine
2. Significant reactions (e.g., Grade 3 AEs) following administration of study vaccine (including severe pain, severe swelling, severe headache, persistent high fever or other severe systemic or local reactions) that, in the opinion of the investigator or sponsor, should preclude further administration of study vaccine
3. The occurrence of an SAE (See Section 10.5.1) related to the study vaccine
4. Receipt of any investigative drug, investigative vaccine or immunosuppressive medication (inhaled or topical corticosteroids are allowed) within 28 days of study vaccine
5. The occurrence of other medical conditions, unrelated to study vaccine that in the opinion of the PI contraindicate administration of study vaccine
6. Moderate or severe unsolicited AEs (clinical events or laboratory tests) that are indicative of new and significant end organ dysfunction and that, in the opinion of the investigator or sponsor, should preclude further administration of study vaccine

### Safety Precautions for Study Personnel

Laboratory safety and blood-borne precautions for all USAMRU-K laboratories are delineated in the following USAMRU-K SOPs:

1) SOP NO. KCL 007: Bloodborne and Infectious Control

2) SOP NO. KCL 006: Hazard Communication and Chemical Hygiene

3) SOP NO. KCL 003: Finger-Prick for Blood Smear

4) SOP NO. KCL 002: Emergency Phlebotomy Safety Procedures

5) SOP NO. KCL 005: Laboratory Hazards and Safety Procedures

## Final and Addendum Efficacy and Safety Analyses and Reports

The “Final Efficacy and Safety Data Report” (FESDR) will reflect the fully blinded period of efficacy surveillance from about SD 71 to about SD 240 (specific days differ among subjects, but all subjects will be surveilled for 169 days = six [28 day] months). This is the formal “Efficacy Follow up Period” (EFP). The FESDR will address the study objectives (Section 5), endpoints (Section 12.1), and test null hypothesis (Section 5.4) for the effect of the test article during the EFP (six months). A cleaned EFP database will be submitted to SCI; SCI will query the data, lock the database, and ultimately distribute the FESDR to the DSMB and all study partners as soon as it is available. No interim analysis will be performed. .

After the completion of the EFP, the study will continue in a partially unblinded manner (for efficacy, immunogenicity, and SAEs) for another 4 months. This period of additional efficacy surveillance lasts from about SD 240 to about SD 364. At the end of this 4 ½ month partially unblinded phase, SCI will receive a cleaned database. Information from this database will be appended to the FESDR.

The FESDR will be conducted on final, cleaned data. It will include sections on intention-to-treat (ITT) analyses and will reflect safety and efficacy surveillance data from SD 0 to SD 240 ~~71).~~ The AEFP data will be analyzed on final, cleaned data and appended to the FESDR.

# CONDUCT OF THE STUDY

## General Study Aspects

### Screening and Enrollment Process

(See also SSP No. MAL036-01: Recruitment and Informed Consent Process, and SSP No. MAL036-02: Screening Day Procedures.)

Recruitment and screening will proceed until 400 subjects are enrolled. Non-coercive means of recruitment will be used according to existing U.S. Army regulations (viz., AR 70‑25 and AR 40-38). Community leaders (assistant chiefs and local village elders) will be formally briefed in their own language on the nature and purpose of the study. They will be allowed to ask questions freely of the PI or his designees. Parents/guardians of prospective subjects will view a videotaped briefing on the nature and purpose of the study and will then receive both oral and written explanations of the study, after which written informed consent will be obtained from at least one parent per subject. No question relating to health will be asked of parents/guardians or children prior to consenting. So that language and illiteracy will not be impediments to informed consent, all such briefings and explanations will be in Dholuo, the local language. All screening tests and procedures (see below) will be performed only after informed consent has been obtained from the parent or guardian.

A record will be prepared for each subject at the screening visit. Source document forms will also serve as the Case Report Forms (CRFs) for this study. The screening forms, which will be labeled with a subject identification (SID) number, will contain information about the subject's date of birth, medical history, physical examination findings, date of screening visit, whether the subject was enrolled, and (where applicable) reasons for exclusion from the study.

Parents of subjects will provide a medical history (with special attention to any history of recurrent infections to suggest immune suppression, previous history of splenectomy, and prior vaccine reactions). Subjects will also undergo physical examination and routine standard laboratory screening tests, which include complete blood count (CBC), creatinine, and ALT. Hemoglobinopathies (sickle cell disease/trait, G6PD deficiency, and alpha-thalassemia) will also be screened. Subjects may be screened one additional time if re-screening after clinical intervention is determined to be necessary (e.g., treatment for malaria). Subjects will be excluded from participation if they meet any of the exclusion criteria (Section 6.5). Subjects excluded from this study because of significant abnormalities will be referred to the local health center for evaluation and treatment. All screening tests will be completed within 45 days prior to entry into the study; laboratory tests may be conducted at other times during the course of the trial if the investigator judges it necessary for the safety of the subject. All subjects randomized into the study will be identified and followed by SID number. All screening and follow-up diagnostic laboratory studies will be performed at the WRP KC laboratory. Information gathered during screening (medical history, physical examination, and laboratory analysis) will be recorded on the CRFs.

A photograph will be taken of each child who is screened, along with the parent/guardian, and stored securely in a computer at WRP KC. The investigator will randomize (see also Section 9.4) 400 eligible subjects who fulfill all the inclusion criteria and none of the exclusion criteria. A picture ID card of each eligible child and parent/guardian will be created using the stored photo, and the ID provided to each parent/guardian. The card will include contact details for study staff to facilitate documentation of medical care received outside the study health facilities. Copies of these pictures will also be kept in the subjects’ records to aid the study staff in confirmation of the child’s identification for future visits. The photos of subjects who are determined ineligible to participate will be deleted from the computer. CRFs will be filled in for all subjects enrolled in the study, and all data collected during the study will be recorded on the CRFs.

### Vaccination Process

On each vaccination day, criteria for continued eligibility will be reviewed and reverified. A history-directed physical examination will be done and axillary temperature, pulse, blood pressure, respirations and baseline general symptom history will be recorded. Venous blood will be collected for laboratory analysis as detailed in Section 8.1.

After the identity of the subject is checked (by comparing the SID number and photograph in subject’s record with the parent/subject’s photo ID), subjects will be vaccinated by intramuscular injection into the left anterolateral thigh muscles unless a compelling reason for using the right anterolateral thigh is evident (See also SSP No. MAL036-04: Vaccination Day Procedures). All vaccinations will be done in a fashion that maintains double-blinding (See Section 9.5.1). The vaccination periods may be up to ten consecutive days, but every effort will be made to vaccinate all 400 children over seven days.

Although all the foregoing study days are provisional (circumstances may require delays of up to two weeks), vaccinations (200 test article recipients, 200 rabies vaccine recipients) will occur on or about Study Days 0 (Dose 1), 29 (Dose 2), and 57 (Dose 3).

### Post-immunization Evaluation Procedures

Immediately after immunization, each subject will proceed to the next station for assessment of local and systemic reactions. Each subject will be observed for at least 60 minutes post-vaccination. Appropriate medical treatment will be readily available in the unlikely case of an anaphylactic reaction following the administration of the vaccine (see Section 9.8.1 and SOP 501.07). Signs and symptoms (pain, swelling, fever [defined as axillary temperature  37.5°C], and irritability/ fussiness) will be solicited from subject and parent and then recorded on the CRF by an evaluator according to adverse events recording procedures as outlined in Section 10.1.3.

Subjects will complete a seven-day (day of vaccination, plus six subsequent days) follow-up after each vaccination (five visits: day of vaccination, plus days 1, 2, 3, and 6 post‑vaccination) at the WRP KC or one of three outlying follow-up centers (see Section 16.3.3). All AEs will be followed until resolution (see Section 10.4). For any solicited signs or symptoms that persist beyond the first six days post-vaccination, the subject will be followed daily until resolution of the adverse event. Anorexia and any unsolicited AEs will be followed until resolution or study conclusion at intervals determined appropriate by the PI. At each visit, the subjects will be evaluated by soliciting post‑vaccination signs and symptoms from the parent and by examination of the injection site. A physical exam will be performed on day 30 (Visit 6). Every effort will be made to ensure parental and subject compliance with visits. However, if a parent and subject do not appear for a scheduled clinic visit, a clinician or nurse will attempt to contact them on the same day. The staff member who contacts the subject will measure vital signs and collect information on any solicited or unsolicited symptoms for the previous 24 hours. If the clinician determines that the subject has experienced a serious adverse event (SAE), appropriate measures will be taken to notify the Local Medical Monitor (LMM), the DSMB, the IRBs, and the sponsor (see Section 10.5.2).

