## Eliciting and Documenting Adverse Events

### Definition of an Adverse Event

Reportable non-serious adverse events (RNAEs) are discussed in Section 10.1.4; serious adverse events (SAEs) are discussed in Section 10.5.

An adverse event (AE) includes any noxious, pathological, or unintended change in anatomical, physiological, or metabolic functions as indicated by physical signs, symptoms, or laboratory test abnormalities occurring in any phase of the clinical study whether associated with the study vaccine and whether considered vaccine-related. This includes an exacerbation of pre-existing conditions or events, intercurrent illnesses, a vaccine or drug interaction, or the significant worsening of a previously documented condition. A symptom present just prior to a first vaccination, and not exacerbated after the vaccination is administered, should not be considered an AE. Similarly, anticipated day-to-day fluctuations of pre-existing conditions,including the disease under study, that do not represent clinically significant exacerbations need not be considered AEs. However, discrete episodes of chronic conditions occurring during a study period (after the first vaccination) should be reported as AEs in order to assess changes in frequency or severity.

AEs should be documented in terms of a medical diagnosis. When this is not possible, an AE will be documented in terms of signs and symptoms observed by the investigator or reported by the participant at each study visit.

Pre-existing conditions, or signs and symptoms (including any that are not recognized at study entry but are recognized during the study period) that are present in a subject prior to the start of the study, should be recorded on the Medical History CRF. Any solicited sign or symptom present during a pre-vaccination assessment should be recorded on the Pre‑Vaccination Assessment CRF.

AEs that occur after informed consent is obtained, but prior to a first vaccination, will be documented on the Medical History CRF.

Any non-elective hospitalization will be considered an SAE, rather than an AE, regardless of the reason for hospitalization and possible causal relationship to vaccine administration (See Section 10.3).

Solicited AEs to be recorded are described in Section 10.1.5. Any other AEs will be recorded as unsolicited AEs.

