### Solicited Adverse Events

Exhibit 11. Solicited Adverse Event (AE) Categories

| Categories | Adverse Events |
| --- | --- |
| Local (injection site) AEs | Pain at the injection site |
| Swelling at the injection site |
| General (systemic) AEs | Fever (i.e., axillary temperature  37.5°C) |
| Irritability/fussiness |
| Loss of appetite |
| Drowsiness |

N.B.: Axillary temperature will be recorded at the time of the clinic visit. Should additional temperature measurements be recorded at another time of day, the highest temperature will be recorded.

The assessment of severity/intensity will be as described in Section 10.2. For general signs and symptoms reported, the investigator will ensure that causality is assigned as described in Section 10.3.

For all signs and symptoms reported, the investigator will ensure that the outcome is reported as described in Section 10.4.

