## Assessment of Intensity

Intensity of solicited AEs will be assessed and graded by an investigator or clinician as presented in Exhibit 12.

| Exhibit 12. Assessment of Solicited Adverse Event (AE) Intensity | | |
| --- | --- | --- |
| **AE** | **Grade** | **Intensity Definition** |
| Pain at injection site | 0 | Absent |
|  | 1 | Minor reaction to touch |
|  | 2 | Cries/protests on touch |
|  | 3 | Cries when limb is moved or spontaneously painful or limping or reluctance to bear weight |
| Swelling at injection site | 0 | Absent |
|  | 1 | < 5 mm |
|  | 2 | 5-20 mm |
|  | 3 | > 20 mm |
| Fever | 0 | < 37.5°C |
|  | 1 | 37.5-38.0°C |
|  | 2 | 38.1-39.0°C |
|  | 3 | > 39.0°C |
| Irritability/Fussiness | 0 | Behavior as usual |
|  | 1 | Crying more than usual/no effect on normal activity |
|  | 2 | Crying more than usual/ interferes with normal activity |
|  | 3 | Crying that cannot be comforted/ prevents normal activity |
| Drowsiness | 0 | Behavior as usual |
|  | 1 | Drowsiness easily tolerated |
|  | 2 | Drowsiness that interferes with normal activity |
|  | 3 | Drowsiness that prevents normal activity |
| Loss of appetite | 0 | Normal |
|  | 1 | Eating less than usual/no effect on normal activity |
|  | 2 | Eating less than usual/interferes with normal activity |
|  | 3 | Not eating at all |

For all other AEs, maximum intensity should be assigned to one of the following categories:

0 = No adverse event

1 = An adverse event that is easily tolerated by the subject, causing minimal discomfort and not interfering with everyday activities.

2 = An adverse event that is sufficiently discomforting to interfere with normal everyday activities.

3 = An adverse event that prevents normal, everyday activities. (Such an adverse event would, for example, prevent attendance at school, church or other typical assemblies, and would necessitate the administration of corrective therapy.)

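### Section 7.1.3 tells staff to solicit four adverse events and sets anorexia apart for follow-up, while Section 10.1.5 and Exhibits 11 and 12 define six, so two systemic events may go unasked or be misfiled

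*Protocol*

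**What the plan says.** Section 7.1.3 (Post-immunization Evaluation Procedures) describes the assessment after injection. It gives a closed list in parentheses of pain, swelling, fever and irritability, ending "fussiness) will be solicited from subject and parent and then recorded on the CRF by an evaluator", and refers the evaluator to Section 10.1.3 for the recording procedure. The next paragraph covers the five visits after each dose. For a solicited sign or symptom that lasts beyond day six, "the subject will be followed daily until resolution of the adverse event". It then adds: "Anorexia and any unsolicited AEs will be followed until resolution or study conclusion at intervals determined appropriate by the PI".

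Section 10.1.5 carries "Exhibit 11. Solicited Adverse Event (AE) Categories", which has two local events (pain, swelling) and four general ones (fever, irritability/fussiness, "Loss of appetite" and drowsiness). Exhibit 12 in Section 10.2 grades all six from 0 to 3. Its Grade 3 for drowsiness, for example, is "Drowsiness that prevents normal activity".

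Section 10.1.1 says which list governs: "Solicited AEs to be recorded are described in Section 10.1.5. Any other AEs will be recorded as unsolicited AEs".

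Three other places use the solicited/unsolicited split without a list of their own:
- Section 12.1.2 makes solicited AEs over seven days a secondary safety endpoint.
- Section 6.9.2 puts all solicited AEs, but only Grade 3 unsolicited AEs, into the report on the first 200 children that precedes the next dose.
- Section 6.9.1 suspends dosing when 20 (5%) or more children have an "occurrence of Grade 3 solicited systemic (not local) AEs judged related to the study vaccine". It applies a second, separate threshold of 20 children to related Grade 3 unsolicited AEs.

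**The concern.** Section 7.1.3 is the conduct text, the part that staff at the clinic and at the three field follow-up centers are most likely to work from. Its list omits loss of appetite and drowsiness, both of them systemic. Its own cross-reference does not supply them: Section 10.1.3 offers one general, non-leading question to the parent and no symptom list.

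A symptom that is asked about at every visit and one that is recorded only when a parent mentions it have different capture rates. If the two omitted events are not prompted, or are prompted by some staff and not by others, the reactogenicity profile for them is incomplete and uneven. If they are recorded but filed as unsolicited, they move to another endpoint and another suspension count. The anorexia sentence adds to this, because it groups one of the six solicited events with the unsolicited ones for follow-up and gives no reason.

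**Working it through.** **1. The two lists.**
- Section 7.1.3: pain, swelling, fever, irritability/fussiness. Four events, of which 4 − 2 local = 2 are systemic.
- Exhibits 11 and 12: the same four plus loss of appetite and drowsiness. Six events, of which 6 − 2 local = 4 are systemic.
- The difference is exactly loss of appetite and drowsiness. Section 7.1.3 names 2 of the 4 systemic events.

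**2. Which list governs.** Section 10.1.1 points to Section 10.1.5 and makes everything else unsolicited. Sections 6.9.1 and 12.1.2 contain no competing list. The endpoint and the suspension count therefore both rest on six events.

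**3. The anorexia sentence.** I take anorexia in 7.1.3 and loss of appetite in Exhibit 11 to be the same event. As a solicited event lasting beyond day six, it falls under daily follow-up. Under the anorexia sentence it is followed at intervals the PI chooses. Both cannot apply. The sentence concerns follow-up frequency only and does not call anorexia unsolicited.

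**4. The threshold.** 0.05 × 400 = 20, which reproduces the 20 (5%) in Section 6.9.1. The choice of list leaves the threshold unchanged. It changes only which events are counted toward it.

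**5. What the protocol's own data show.**
- Mal-031, Exhibit 4b, 50 µg, any grade: fever 16 (53%), loss of appetite 14 (47%), irritability 2 (7%), drowsiness 0. Comparator: loss of appetite 5 (33%). The exhibit heads these columns with 84 and 42 doses, but the percentages fit 30 and 15 children (14/30 = 47%, 5/15 = 33%). Section 7.1.3 thus names irritability and omits a reaction that was much more frequent at the dose level used here.
- Mal-031, Grade 3: loss of appetite 0 in every group, and no drowsiness of any grade. On these data the four-event and six-event suspension counts are identical.
- Mal-020, Exhibit 2 (same adjuvant, different antigen, ages 1 to 5 years), related Grade 3 entries summed over the three RTS,S/AS02A groups: loss of appetite 0 + 2 + 2 = 4, irritability 0 + 0 + 3 = 3, fever 0 + 1 + 0 = 1, drowsiness 0. Loss of appetite is 4 of 8. These are per-dose entries and may overlap within a child.

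**6. Illustration of the suspension count (assumed rates).** Let the pooled chance per child of a related Grade 3 fever or irritability be 3%, and of a related Grade 3 loss of appetite or drowsiness be b, with no overlap. The chance of 20 or more among 400 children is the upper binomial tail.

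| b | all four systemic events in one count | fever and irritability only |
|---|---|---|
| 0% | 0.02 | 0.02 |
| 1% | 0.18 | 0.02 |
| 2% | 0.53 | 0.02 |
| 3% | 0.83 | 0.02 |

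At b = 2%, the two misfiled events alone would reach 20 with probability 0.0002, so the separate unsolicited count would not make up the loss. The first row is the situation Mal-031 points to.

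**The case against.** The strongest reply is that the protocol already settles the matter. Section 10.1.1 fixes the definition, Section 10.1.6 treats unsolicited events as those other than the solicited ones, and Exhibit 12 grades all six. The four-item list stands beside the 60-minute observation. The later-visit text in 7.1.3 speaks of soliciting post-vaccination signs and symptoms with no restriction, and the visit schedule in 7.2 simply calls for solicited and unsolicited AEs to be recorded. The CRF and the study-specific vaccination-day procedure are not shown and may well prompt for all six.

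Much of this stands. A reader might infer that the endpoint and the suspension rule are defined differently in different sections. They are not, because Section 10.1.1 governs and neither 6.9.1 nor 12.1.2 offers a rival list. A reader might also infer that anorexia has been reclassified as unsolicited. The sentence does not say so. It names anorexia separately, and an exception to daily follow-up is needed only if anorexia is otherwise solicited. Finally, a reader might derive from Mal-031 a definite understatement of systemic reactogenicity. The marginal counts do not allow it: depending on overlap with fever, adding loss of appetite could raise the share of children with any systemic event by anything from 0 to 14 of 30 at 50 µg, and from 0 to 5 of 15 on the comparator.

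The reply does not remove the mismatch. Vaccination day is one of the five visits that count toward the solicited-AE endpoint, so a four-item list there is a gap even on the narrow reading. The cross-reference in 7.1.3 leads to a section without a list. The anorexia exception and the daily rule still conflict.

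**Conclusion.** The point holds as an operational inconsistency. Section 7.1.3 names four events and follows anorexia differently, while the governing definition has six. The formal definitions of the endpoint and of the 6.9.1 count are intact. What is exposed is whether loss of appetite and drowsiness are asked about every time and filed correctly.

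If they are filed as unsolicited, Grade 1-2 cases leave the pre-dose report as Section 6.9.2 describes it, and Grade 3 cases fall into the separate unsolicited count. The first consequence rests on 6.9.2, since Section 13.2 describes that report more narrowly, as SAEs and Grade 3 AEs.

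No numerical effect on this trial can be claimed. Loss of appetite was common in Mal-031, so capture matters for the reactogenicity profile. With no Grade 3 loss of appetite and no drowsiness there, those data give no change in the suspension count. The Mal-020 entries show only that such Grade 3 events can occur with this adjuvant. The conclusion assumes that some staff or forms follow the text of 7.1.3, which the protocol alone cannot confirm or exclude.

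**What to change.** In Section 7.1.3, replace the four-item parenthesis with a reference to the solicited AEs of Exhibit 11, applied at all five visits after each dose, and send the evaluator to Section 10.1.5 as well as 10.1.3. Reconcile the anorexia sentence with the daily follow-up rule for persisting solicited symptoms, either by removing the difference or by stating that it is intended and why. Which follow-up interval is appropriate is for the investigators to decide. Whatever they decide, add one sentence saying that loss of appetite counts as a solicited AE for analysis and for the Section 6.9.1 count, as Section 10.1.1 already implies. Check that the CRF prompts for all six events.

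The cost is a wording change and, at most, two more questions at visits that already take place, using grades that Exhibit 12 already provides.
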